## Abstract

**Background:**

Postural orthostatic tachycardia syndrome (POTS) is an autonomic nervous system disorder causing an abnormal cardiovascular response to upright posture. It affects around 0.2% of the population, most commonly women aged 13 to 50 years. POTS can be debilitating; prolonged episodes of pre-syncope and fatigue can severely affect activities of daily living and health-related quality of life (HRQoL). Medical treatment is limited and not supported by randomised controlled trial (RCT) evidence. Lifestyle interventions are first-line treatment, including increased fluid and salt intake, compression tights and isometric counter-pressure manoeuvres to prevent fainting. Observational studies and small RCTs suggest exercise training may improve symptoms and HRQoL in POTS, but evidence quality is low.

**Methods:**

Sixty-two people (aged 18–40 years) with a confirmed diagnosis of POTS will be invited to enrol on a feasibility RCT with embedded qualitative study. The primary outcome will be feasibility; process-related measures will include the number of people eligible, recruited, randomised and withdrawn, along with indicators of exercise programme adherence and acceptability. Secondary physiological, clinical and health-related outcomes including sub-maximal recumbent bike exercise test, active stand test and HRQoL will be measured at 4 and 7 months post-randomisation by researchers blinded to treatment allocation. The PostUraL tachycardia Syndrome Exercise (PULSE) intervention consists of (1) individual assessment; (2) 12-week, once to twice-weekly, supervised out-patient exercise training; (3) behavioural and motivational support; and (4) guided lifestyle physical activity. The control intervention will be best-practice usual care with a single 30-min, one-to-one practitioner appointment, and general advice on safe and effective physical activity. For the embedded qualitative study, participants (*n* = 10 intervention, *n* = 10 control) will be interviewed at baseline and 4 months post-randomisation to assess acceptability and the feasibility of progressing to a definitive trial.

**Discussion:**

There is very little high-quality research investigating exercise rehabilitation for people with POTS. The PULSE study will be the first randomised trial to assess the feasibility of conducting a definitive multicentre RCT testing supervised exercise rehabilitation with behavioural and motivational support, compared to best-practice usual care, for people with POTS.

**Trial registration:**

ISRCTN45323485 registered on 7 April 2020.

## Background

Postural orthostatic tachycardia syndrome (POTS) affects the autonomic nervous system resulting in an abnormal cardiovascular response to upright posture. It is defined as a clinical syndrome that is usually characterised by (1) frequent symptoms that occur with standing such as light-headedness, palpitations, tremulousness, generalised weakness, blurred vision, exercise intolerance and fatigue; (2) an increase in heart rate of ≥ 30 beats per minute when moving from a recumbent to a standing position held for more than 30 s; and (3) the absence of orthostatic hypotension (> 20 mmHg drop in systolic blood pressure) [1]. The pathophysiology of POTS is multi-factorial. Symptoms may result from a multitude of mechanisms, including but not limited to volume depletion, immune dysfunction or autoimmune disease, cardiac and physical deconditioning and the inability of lower limb vasoconstriction to compensate for postural blood volume shifts [2]. A disproportionate autonomic response, aimed at rectifying haemodynamic compromise, results in the hallmark features of prolonged pre-syncope (feeling of being about to faint) and fatigue [1, 3].

POTS can be debilitating; simple activities may result in persistent orthostatic intolerance. This can lead to poor concentration, palpitations, nausea, ‘brain fog’ and exercise intolerance [3] affecting activities of daily living and health-related quality of life (HRQoL) [4]. Hypermobility spectrum disorders (HSD) are a common comorbidity [5]. The ability to attend education, undertake gainful employment and care for dependants can be substantially compromised by POTS. A constellation of symptoms can initiate a negative feedback loop by which enforced inactivity further precipitates orthostatic intolerance, immobility and deconditioning [6, 7].

Treatment for POTS is limited; medical therapies have not been tested in randomised controlled trials (RCTs) [8]. According to expert consensus, non-pharmacological therapy is first-line treatment [1]. Conservative measures include increased fluid and salt intake, compression tights, isometric counter-pressure manoeuvres (e.g. hand gripping and leg crossing/tensing) to prevent fainting, and psychological interventions to help manage chronic illness [1]. Exercise training is also advocated as an essential component of POTS treatment [1]. However, this is based on only two small studies, one of which excluded people with HSD [9] and one which investigated orthostatic intolerance in military recruits [10]. These studies demonstrated some physiological improvement (increased left ventricular mass/blood volume and decreased standing heart rate), reduced symptoms and improved HRQoL. More recently, a prospective observational study (*n* = 251) enrolled people with POTS on 3 months of unsupervised community exercise [8]. A total of 103 people completed the treatment, of which 73 no longer met the diagnostic criteria for POTS, and HRQoL was improved. However, the study was limited by the lack of a control group, and poor individualisation and supervision of exercise, leading to 60% attrition.

### Rationale for a trial

Supervised exercise rehabilitation may be an effective therapy for POTS, with resultant clinical and psychosocial benefit. Observational studies, whilst not definitive, suggest that symptoms and psychosocial morbidity may improve [8]. Based on this preliminary evidence, it is important to investigate whether or not people with POTS can benefit from supervised exercise rehabilitation. The broad spectrum of physical ability, symptoms and comorbidities requires that this be initially undertaken within well-designed clinical trials that take account of previous research limitations. The first step is to investigate the feasibility of conducting a multi-centre RCT testing a comprehensive exercise rehabilitation intervention, compared to best-practice usual care, for people with POTS.

## Methods/design

### Aim

The aim of the PostUraL tachycardia Syndrome Exercise (PULSE) study is to assess the feasibility of conducting a multi-centre RCT testing a supervised exercise rehabilitation intervention with behavioural and motivational support (PULSE intervention) compared to best-practice usual care for people with POTS.

### Objectives

#### Undertake a feasibility RCT:

Sixty-two participants (*n* = 31 intervention, *n* = 31 control) will be randomised to the PULSE intervention or control. Process-related measures will include eligibility, recruitment, uptake and intervention adherence. Physiological, clinical and health-related measures will include a sub-maximal graded recumbent bike exercise test, active stand test and HRQoL.

#### Conduct a qualitative analysis:

To explore perceptions, opinions, acceptability and experiences of trial procedures, the PULSE intervention and outcome measures, interviews will be conducted with a sample of participants, drop-outs, and those who declined participation.

### Study design and setting

PULSE is a two-arm feasibility RCT with an embedded qualitative study (Fig. 1). Recruiting simultaneously from two NHS POTS clinics in England (University Hospitals Coventry & Warwickshire (UHCW) NHS Trust and Imperial College Healthcare NHS Trust), participants will be randomised to the intervention or control arms in a ratio of 1:1, stratified by NHS Trust. Table 1 summarises study methods and design in accordance with the World Health Organization (WHO) Trial Registration Data Set.

**Fig. 1 Fig1:**
[figure not shown]
Study flow chart

**Table 1 Tab1:** World Health Organization trial registration data set

Data category	Information
Primary registry and trial identifying number	ISRCTN45323485
Date of registration in primary registry	7 April 2020
Secondary identifying numbers	REC reference: 20/EM/0077 BHF reference: PG/19/22/34203
Source(s) of monetary or material support	British Heart Foundation Project Grant
Primary sponsor	UHCW NHS Trust University Hospital [name] [contact] Email: R&[contact]
Secondary sponsor(s)	Coventry University [name] Email: [contact]
Contact for public queries	Coventry University [name] Email: [contact]
Contact for scientific queries	[name] Coventry University/UHCW NHS Trust [contact] Email: [contact]
Public title	Supervised exercise rehabilitation for people with postural tachycardia syndrome
Scientific title	PostUraL tachycardia Syndrome Exercise (PULSE): a randomised controlled feasibility study
Countries of recruitment	England
Health condition(s) or problem(s) studied	Postural orthostatic tachycardia syndrome
Intervention(s)	Intervention group: (1) individual assessment, (2) supervised out-patient exercise programme, (3) behavioural and motivational support, (4) guided lifestyle physical activity. Control intervention: best-practice usual care
Key inclusion and exclusion criteria	Inclusion: adults (18–40 years) with confirmed diagnosis of POTS and attending syncope out-patient clinics; able to attend a PULSE centre; able to provide informed consent. Exclusion: absolute contraindications to exercise; currently achieving CMO physical activity guidelines; mental health issue preventing engagement with trial procedures; pregnant at time of recruitment; previous randomisation in PULSE; unable to attend a PULSE centre; took part in PULSE intervention co-creation.
Study type	Type: feasibility, interventional, two-centre Allocation: randomised Assignment: parallel Masking: outcomes assessors, chief investigator, statistician
Date of first enrolment	TBC
Target sample size	62
Recruitment status	Ready to start recruitment (on hold due to Covid-19)
Primary outcome(s)	Feasibility and process indicators: number of patients screened, eligible, recruited, randomised, withdrawn and retained; adherence to exercise rehabilitation programme; length of time to complete each outcome assessment and the whole outcome assessment appointment; willingness of participants to join non-POTS specific exercise rehabilitation programmes; physiological, clinical, patient-reported outcomes to identify a primary outcome for a definitive trial; acceptability of the interventions and the trial (qualitative interviews)
Key secondary outcomes	At 4 and 7 months: exercise capacity—graded recumbent cycle ergometer test; autonomic function—increase in heart rate from supine to 10-min stand; symptom burden—COMPASS 31 dysautonomia scale and fatigue severity scale; HRQoL—EQ-5D-5L; self-efficacy—general self-efficacy scale; exercise tolerability—continuous heart rate monitoring and symptoms during exercise; adverse events. At baseline and 7 months: semi-structured interviews with participants

### Eligibility criteria

People with POTS meeting the study inclusion criteria are eligible to participate (Table 2).

**Table 2 Tab2:** Inclusion and exclusion criteria

Inclusion criteria	Exclusion criteria
▪ Adults 18 to 40 years of age ▪ Confirmed diagnosis of POTS [1] and currently attending specialist out-patient clinics ▪ Able to attend a PULSE centre 1–2 times/week for 8–12 weeks for exercise training ▪ Able to provide informed consent	▪ Absolute contraindications to exercise as per international clinical guidelines [11, 12] ▪ Any serious mental health/cognitive issue that will prevent engagement with study procedures or increase the risk of exercise complications ▪ Unable to make suitable travel arrangements ▪ Currently undertaking structured exercise/physical activity equivalent to the Chief Medical Officer (CMO) guidelines (150 min moderate exercise per week or 60 min vigorous per week) ▪ Previous randomisation in the present trial ▪ Pregnancy ▪ Taken part in co-creation workshops to design the PULSE intervention/study

### Participant identification, recruitment and informed consent

Physicians, arrhythmia nurse specialists or other clinical staff involved in the care of people with POTS will identify eligible participants from two sources: (1) specialist nurse/medical POTS out-patient clinics, (2) local secondary care disease registers. Participant information leaflets will be provided in person during an out-patient clinic appointment or will be sent in the post with a request to return an expression of interest form. Once interest and willingness to be contacted have been confirmed, participants will be contacted by a member of their clinical team and invited to attend a baseline assessment appointment, at which eligibility will be reassessed and informed consent taken. The PULSE study requires different levels of consent: (1) to take part in the trial; (2) for medical notes to be reviewed by designated individuals and personal identifiable information to be securely stored; and (3) to allow telephone contact between the trial team and the participant or designated next of kin.

### Randomisation, allocation concealment and blinding

After all baseline assessments have been completed, participants will be randomised on a 1:1 basis to intervention or control, stratified by centre (UHCW NHS Trust or Imperial College Healthcare NHS Trust) (Fig. 2). Randomisation will be performed, and allocation concealment maintained, using an online validated randomisation sequence generator, as part of an electronic data capture system (Castor). Only PULSE practitioners, who will be delivering either the control or active interventions, will be informed of group allocation, and only after all baseline measures are complete. Participants and practitioners cannot be blinded to group allocation. PULSE practitioners will deliver both the active and control interventions, so will be aware of treatment allocation after randomisation. Outcome assessment staff, the chief investigator (CI) and the trial statistician will be blinded to group allocation, until statistical analysis is complete.

**Fig. 2 Fig2:**
[figure not shown]
Schedule of enrolment, interventions and assessments

### Interventions

#### The PULSE intervention

To ensure applicability and acceptability further to receipt of study grant funding, the intervention was refined and finalised using co-production methods, in accordance with INVOLVE [13]. A detailed account of this process will be available in an intervention development publication. Briefly, two workshops with patients, public and stakeholders were led by experienced facilitators. During the first workshop, proposed outcome measures and the PULSE intervention were presented to the group and discussed from all stakeholders’ perspectives. Interim work was then undertaken by the research team to refine the intervention components and outcome measures prior to workshop two during which the protocol was finalised and implementation and delivery were discussed.

POTS patients and stakeholders (family, nursing, psychology, exercise physiology, physiotherapy, general practice, POTS UK) attended the meetings to ensure that contributions were correctly interpreted [14]. Co-production techniques allowed these multiple stakeholders to work towards a common goal [13]. It was a flexible and adaptable process, using multiple communication strategies, to ensure inclusion of people who were affected differently by POTS. The process was iterative, with each session informing the next, until a solution was achieved. Researcher notes were analysed thematically, thus informing the refinement and implementation of the PULSE intervention and study [15].

##### Format:

To ensure external validity to the NHS out-patient/community outreach setting, the PULSE intervention is based on existing UK cardio-pulmonary rehabilitation guidelines and service design [16–18].

##### Programme design:

Participants randomised to the PULSE intervention will either (1) access existing cardiopulmonary rehabilitation programmes, i.e. they will exercise with people with a range of cardiopulmonary conditions, as well as other trial participants randomised to the PULSE intervention, or (2) they will attend dedicated sessions for people with POTS. To encourage peer support, every effort will be made to ensure there are at least two to three PULSE participants exercising at the same centre at the same time. The PULSE intervention has four components:

#### Component 1: individual assessment and exercise familiarisation

##### Individual assessment:

Participants will undergo a 1-h, one-to-one appointment with a PULSE ‘practitioner’ (clinical exercise physiologist), to assess and record medical and physical activity history and medication and to discuss goals, expectations and any concerns.

##### Exercise prescription:

There are no accepted guidelines for exercise training in POTS. The intervention will be individualised and is based on existing evidence, patient and public involvement (PPI) and co-production sessions and the centres’ expertise in the provision of exercise for clinical populations. As such, the PULSE practitioner will prescribe a safe and effective individualised exercise programme [11, 17] based on clinical information, data from graded, sub-maximal cycle ergometry and active stand tests and patient-centred goal setting.

##### Familiarisation sessions:

Exercise instruction will be provided on an individual basis during two one-on-one familiarisation sessions in the first week of the programme, and reinforced throughout, by PULSE practitioners and clinical staff. Familiarisation sessions, conducted within the cardiopulmonary rehabilitation programmes, will enable participants to build confidence, whilst PULSE practitioners refine and optimise the exercise prescription. Behavioural and motivational support will also be introduced during these sessions.

#### Component 2: supervised out-patient exercise programmes

For the first 6 (of 12) weeks, exercise will be undertaken during one to two sessions per week solely in a controlled gym environment with carefully staged progression in response to participant tolerance and symptoms. For those that are able, moderate intensity dynamic cardiovascular exercise will be prescribed. In addition, ‘functional fitness training’ will aim to improve orthostatic tolerance and general musculoskeletal deconditioning. This type of training is targeted specifically at the components of physical fitness required for activities of daily living, making use of multi-plane motion, to improve agility, coordination, proprioception, balance and functional strength.

##### Prescribed exercise:

Exercise will be versatile and individualised, incorporating cardiovascular and functional resistance training components. Interval or continuous cardiovascular exercise will be performed at a tolerable intensity (regulated with rating of perceived exertion [RPE] and symptoms) for a manageable time, focusing initially on exercises in the recumbent or semi-recumbent position (e.g. rowing machine, recumbent cycle ergometer) to minimise orthostatic tachycardia. Gentle warm-up and cool down will be performed in the manner best suited to individual symptoms. Exercise intensity and time will be gradually increased, and upright exercise introduced as tolerated.

#### Component 3: behavioural and motivational support

Comprehensive behavioural change and motivational strategies to improve adherence and compliance to exercise will be incorporated into the PULSE intervention. Every second week, before or after their supervised exercise session, participants will receive a one-to-one, 30-min behavioural and motivational session delivered by a trained PULSE practitioner, with the aim of improving short- and long-term adherence to exercise.

The PULSE intervention will be based on a cognitive behavioural framework including self-efficacy and self-management principles with behaviour change theory [19]. In particular, the COM-B model of behaviour change (‘capability’, ‘opportunity’, ‘motivation’ and ‘behaviour’) will be applied to the content and delivery of the behavioural sessions. Capability relates to increasing confidence through supervised exercise practice and exploring participants’ own health beliefs and perceived barriers which may prevent them from progressing with the intervention. For example, quite often people with POTS may avoid certain activities and movement due to a fear of aggravating symptoms [20]. Opportunity, both internal and external to the individual, will be explored through beliefs and thoughts in relation to knowledge and acceptance of POTS, including principles of self-management and skills of living with what is sometimes termed ‘the invisible condition’. Access to material and information covered in the sessions will be ensured by producing a participant handbook to allow consolidation of learning and reflection in between sessions. Motivation will also be key to sustained behaviour change for people with POTS. This will be addressed with planning, goal setting and exploration of expectations, with opportunity for self-reflection and discussion of progress, setbacks and overcoming obstacles [21]. This will be combined with the theory of planned behaviour [22, 23] to explore participant’s perceived control, intention and motivation to adhere to the PULSE intervention.

The PULSE practitioners will be trained to use open questions and motivational interviewing to assess participants’ current beliefs and encourage behaviour change. In accordance with existing literature, it will be important to manage expectations. Previous work in POTS has indicated that symptoms may worsen for 4–6 weeks before a lasting benefit is gained [21].

#### Component 4: lifestyle physical activity

Half-way through the supervised exercise intervention, thus after 6 weeks of centre-based exercise has been safely completed, and/or individual exercise tolerance has been evaluated, participants will be encouraged to undertake self-directed, lifestyle physical activity at home in addition to the supervised sessions. This will help ensure that exercise is performed every other day. Activities such as swimming, walking and cycling will be encouraged for those in whom it is appropriate.

#### Control intervention: best practice usual care

Participants in the control arm will be provided with freely available advice on lifestyle physical activity (POTS UK website) [24] during a one-to-one session, lasting approximately 30 min, with a PULSE practitioner. They will not receive any further input during the control intervention period. Participants will be permitted to continue with any current physical activity but will not receive supervised exercise training or behavioural and motivational sessions from PULSE practitioners.

### Safety

The PULSE intervention will be delivered in cardiopulmonary rehabilitation units with qualified staff and appropriate emergency equipment. Lifestyle physical activity will be lower intensity and replicate exercises performed in the gym under supervision. Intervention practitioners will be clinical exercise physiologists, experienced in assessment, prescription and delivery of exercise in clinical populations and trained in the standardised delivery of the PULSE intervention. Additional training in exercise modification to avoid joint subluxation and dislocation in hypermobile participants will be provided by a specialist physiotherapist.

### Primary outcome

The primary outcome will be overall feasibility and process-related measures:
Number of patients screened, eligible, recruited, randomised, withdrawn and retained.Adherence to exercise rehabilitation programme—number of supervised exercise and lifestyle physical activity sessions completed over 12 weeks.Length of time to complete each outcome measure and the whole outcome assessment appointment.Willingness of participants to join non-POTS specific exercise rehabilitation programmes (i.e. standard cardiopulmonary rehabilitation programmes). Participant preference will be recorded, and uptake to each programme model monitored.Physiological, clinical, patient-reported outcomes to confirm/identify a primary outcome for a definitive trial.Acceptability of the interventions and the trial (embedded qualitative study).

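### Adherence is defined as a raw session count that is not tied to the prescribed schedule, so it shows dose received but not the share of the programme followed

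*Protocol article*

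**What the plan says.** All references are to the protocol article.

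- **The measure.** The Primary outcome section lists adherence among the feasibility and process measures and words it as the "number of supervised exercise and lifestyle physical activity sessions completed over 12 weeks". It does not say whether the two kinds of session are added together, and no section sets completed sessions against planned or offered ones.
- **Supervised frequency.** The Abstract (Methods) describes "12-week, once to twice-weekly, supervised out-patient exercise training". Component 2 says: "For the first 6 (of 12) weeks, exercise will be undertaken during one to two sessions per week", with "carefully staged progression in response to participant tolerance and symptoms". Table 2 (Eligibility criteria) asks that participants can attend 1–2 times a week for 8–12 weeks.
- **Prescription.** Under Exercise prescription, the "PULSE practitioner will prescribe a safe and effective individualised exercise programme". The two familiarisation sessions in week 1 build confidence "whilst PULSE practitioners refine and optimise the exercise prescription".
- **Lifestyle activity.** Component 4 says that, about half-way through, "participants will be encouraged to undertake self-directed, lifestyle physical activity at home in addition to the supervised sessions". The only indication of frequency is an aim: "This will help ensure that exercise is performed every other day".
- **Use of the result.** Data analysis foresees descriptive statistics by centre and arm, estimates with 95% confidence intervals and no hypothesis tests. No adherence threshold is given.

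**The concern.** Adherence asks how much of what was asked of participants they did. With a single fixed schedule, a count of completed sessions answers that, because everyone shares the same denominator. Here the supervised schedule can differ twofold within the stated range, and the programme is individualised and staged to tolerance. A low count can then mean missed sessions or a lighter programme fully attended. These lead to different conclusions about a definitive trial: the first points to a problem with acceptability or access, the second to a lower deliverable dose.

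The question is central to this study. The Background criticises an earlier unsupervised programme for poor individualisation and supervision and links this to 60% attrition. Whether patients can follow a supervised, individualised programme is therefore one of the main things PULSE should show. The same ambiguity would affect the planned summary by centre, since two centres with different mixes of weekly frequency could show the same count with different attendance. Dated schedule changes are hard to reconstruct afterwards, so the denominator has to be recorded as it arises.

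**Working it through.** The article gives no figure for planned sessions or for expected adherence, so there is nothing of its own to reproduce. The check is what a given count would mean under the stated schedule.

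**1. Range of a full supervised schedule** (Abstract, Component 2)

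Planned sessions = sessions per week × weeks.
- Once weekly: 1 × 12 = 12
- Twice weekly: 2 × 12 = 24
- If the 8 weeks at the lower end of Table 2 could apply: 1 × 8 = 8, so the range would be 8 to 24

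**2. What 12 completed supervised sessions would mean**
- Frequency set per participant (an assumption): 12/12 = 100% of a once-weekly plan, 12/24 = 50% of a twice-weekly plan.
- Frequency only a permitted range: 12 equals the minimum and is 12/24 = half the maximum.
- If the two week-1 familiarisation sessions count as supervised sessions, a once-weekly course is 2 + 11 = 13, and 13/24 = 54%. The picture hardly changes.

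**3. At arm level** (mix of frequencies not stated; equal attendance in both groups assumed)

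Let p be the share on two sessions a week and a the proportion attended. The mean count is 12(1 + p)a, so at a mean of 12, a = 1/(1 + p).

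| p | 0% | 25% | 50% | 75% | 100% |
|---|---|---|---|---|---|
| a | 100% | 80% | 67% | 57% | 50% |

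**4. Lifestyle sessions**

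If the alternate-day aim is treated as a target for weeks 7–12 (an assumption; Component 4 lets the start depend on tolerance), there are 42/2 = 21 exercise days. Taking off the supervised sessions leaves 21 − 6 = 15 (once weekly) or 21 − 12 = 9 (twice weekly). Even on that reading the expected lifestyle number depends on the supervised frequency, so adding the two kinds of session would not remove the ambiguity.

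**5. Which denominator to use**

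Take a participant who attends 14 supervised sessions and whose frequency changes after week 6.
- Cut from two to one a week: 12 + 6 = 18 scheduled; 14/18 = 78%. Against the initial schedule: 14/24 = 58%.
- Raised from one to two a week: 6 + 12 = 18 scheduled; 14/18 = 78%. Against the initial schedule: 14/12 = 117%.

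The dated schedule gives a sensible proportion in both cases but hides the cut. Showing the initial-schedule proportion beside it reveals the cut.

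**6. Early leavers**

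A participant on two sessions a week who attends every session for 6 weeks and then leaves has 12/12 = 100% if the schedule stops at departure, and 12/24 = 50% if the remaining sessions count as not attended. The second is the one that informs feasibility.

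**The case against.** The strongest objection is that this is a condensed article. Denominators, session logs and separate tabulation commonly sit in a full protocol, an analysis plan or the case report form, none of which is shown. The same list also gives bare numbers screened, recruited and retained, and nobody would take that to rule out rates. A count of completed sessions does not prevent its being reported against a prescription. This has force, and it means that one cannot say the trial will lack a denominator. However, the article does not leave adherence open: it gives the measure a definition, and that definition followed as written does not yield adherence.

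Second, a reader might infer that there is no reference schedule at all. The article does not support that. It gives one to two supervised sessions over 12 weeks, an individual prescription and an alternate-day aim. What is missing is a stated link between these and the count.

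Third, a reader might take the 100% versus 50% contrast as established. It requires frequency to be fixed for each participant, which is a reading of the range together with the individualised prescription and is not stated. A permitted range fits the text equally well. The arm-level and lifestyle figures rest on further assumptions and are illustrations only.

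Fourth, in a programme staged to tolerance, the number of sessions completed is a legitimate feasibility measure in its own right, and a denominator that shrinks with each cut can flatter adherence. Both points are right. The raw count should stay, and the proportion needs the safeguards in steps 5 and 6 of the working.

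**Conclusion.** The point holds in a limited form. As defined, the adherence indicator measures dose received and cannot tell non-attendance from a lighter prescription. The size of the ambiguity is up to a factor of two for supervised sessions over 12 weeks (12 to 24 planned), and a factor of three if the shorter duration in Table 2 applies (8 to 24). For lifestyle sessions no planned number is given.

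It would go too far to infer that the feasibility assessment fails or that a progression decision would be wrong. Withdrawal and retention counts, the interviews and the ADePT framework also inform that decision, and no stated estimate or sample size depends on the measure. Nor does the article say that supervised and lifestyle sessions will be summed; it leaves this open. This is a worthwhile, inexpensive improvement and not a flaw in the design.

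**What to change.** - **Log the denominator.** For each participant randomised to the intervention, record the number of supervised sessions scheduled, with dated changes and reasons, and state whether the week-1 familiarisation sessions count.
- **Keep everyone in.** Include all participants randomised to that arm. Count those who never start or leave early as attending none of the remaining sessions on their initial schedule, or on the once-weekly minimum if none was set.
- **Report the proportion.** Define adherence as supervised sessions attended divided by supervised sessions scheduled, with a 95% confidence interval that treats the participant as the unit. Show the proportion against the initial schedule beside it, so that down-titration does not pass as good adherence.
- **Separate the components.** Report lifestyle sessions as their own count, and keep the raw supervised count, labelled as dose received.

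The cost is one extra logged field and a short addition to the outcome definition, with no effect on sample size or visits. According to Trial status, recruitment had not begun when the article was written, so on the article's own account logging could start with the first participant.
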